### Objectives

The main objective of the POXIPEN trial is to assess the efficacy of IVO vs placebo on maximal bladder capacity in children with neurogenic bladder secondary to myelomeningocele (spina bifida), performing intermittent catheterisation, and for whom oral anticholinergic therapy has been deemed ineffective or associated with adverse effects.

Secondary objectives are:
To assess evolution of maximum bladder pressure after IVO (or placebo);To assess incontinence (i.e., time to clinical failure of treatment as perceived by the patient) after IVO (or placebo);To describe treatment tolerance and adverse effects;To assess the number of responders and continent patients after IVO (or placebo);To assess usability of IVO;To assess changes in patients’ quality of life after IVO (or placebo);To describe changes in patients’ voiding diary data after IVO (or placebo);To describe changes in urodynamic and in renal ultrasound parameters after IVO (or placebo);To identify patients’ characteristics associated with a greater likelihood of responding to IVO.

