Randomisation will be performed by a centralised computer program, stratified by age group (6–11 years, ≥12 years) with the use of a permuted block design of size 10. Patients will be randomised to IVO vs placebo with a 1:1 allocation.

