### Sample Size

Schröder et al. [11] found a 32% increase in maximum bladder capacity in adults using IVO compared with baseline values (*P* < 0.001). In our target population, Raes et al. [29] found a 33% increase in maximum bladder capacity when treated with tolterodine. As patients included in our study already use catheterisation, there is no reason to expect a strong placebo effect from instillation. Given the lack of precise data on the effect of IVO in our target population and based on experts’ opinion, we expect a 33% increase in maximum bladder capacity in the treated group, a 5% increase in the placebo group, a mean (SD) initial bladder capacity of 170 (80) mL, and a correlation between measurements for the same patient of 0.8. To obtain a power of 0.9 with a type I error risk set at 0.05, 26 patients per group are needed. To allow for a margin of error, we rounded up the total expected sample size to 60.

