### Statistical Analyses

For the primary outcome, an intention‐to‐treat analysis will be conducted to assess the difference between the two groups in the evolution of maximum bladder capacity, using a linear mixed model accounting for repeated measurement, age stratification, and treatment exposure as a binary variable. A secondary exploratory analysis will be conducted to account for any imbalance that may occur between groups despite randomisation due to the small sample size. Multivariate linear regression will be performed, adjusted for age and gender.

Given the small sample size and the short duration of follow‐up for each patient, there should be little or no missing data. For the primary outcome, patients lost to follow‐up will be assigned the value measured during the last cystomanometry performed (i.e., last observation carried forward).

No intermediate analysis is planned given the small sample size.

Two secondary outcomes will be analysed following a fixed sequence in a priori ordered hypotheses:
Maximum bladder pressure after 4 weeks of treatment: the two groups will be compared using the same methodology as for the primary outcome;Time to treatment failure: the two groups will be compared using a two‐tailed log‐rank test. If a patient is lost to follow‐up, the date of treatment failure will be the date of last news plus 1 day.

Occurrence of AEs will be compared in the two groups using a Fisher's test with a significance threshold = 0.05.

The proportions of responders and continent patients after 4 weeks of treatment will be calculated with their 95% CI.

Standardised differences in patients’ quality of life assessed with the KIDSCREEN‐10 and ICIQ‐UI‐SF questionnaires will be compared between the two groups using a Wilcoxon test, with a significance threshold = 0.05. As recommended by the KIDSCREEN‐10 developers, an additional subgroup analysis will be performed to distinguish children aged 6–7 years from those aged 8–17 years.

Changes in voiding diary elements, urodynamic parameters, and renal ultrasound parameters after 4 weeks of treatment will be compared using a Wilcoxon test, with a significance threshold = 0.05.

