### Implications

The POXIPEN trial will be the first RCT to evaluate the efficacy of IVO on neurogenic bladder in children. It should provide a high level of evidence of the benefit of IVO in this patient population. If IVO proves effective in improving maximal bladder volume and pressure, it could lengthen the delay in therapeutic escalation to intravesical onabotulinumtoxinA injection, thereby reducing the risk of complications associated with general anaesthesia in children. Besides, reducing the incidence of bladder leakage could improve patients’ quality of life. For ethical and regulatory reasons, our study population is limited to children aged ≥6 years. If efficacy and safety are demonstrated in this population, future studies should be designed to evaluate IVO in younger children, who represent an important target population. From an individual point of view, if IVO is effective for a patient during the study, it will be possible for the referring investigator to prescribe this treatment as part of a compassionate use after the study. The French regulatory framework could then evolve towards a marketing authorisation by health authorities, thus changing the way paediatric patients with neurogenic bladder disease are managed.

A long‐term evaluation of this treatment, including a medico‐economic evaluation, could be carried out in a second phase, following completion of this study.

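### The only analysis stated for adverse-event occurrence is a Fisher test at 0.05 with no estimate or interval; at 30 children per arm a non-significant result could not support a statement that safety was demonstrated.

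*Protocol article*

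**What the plan says.** All places are in the protocol article.

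- **Objectives** sets a descriptive safety aim: "To describe treatment tolerance and adverse effects".
- **Endpoints** defines the outcome as the occurrence of AEs and their time of onset, and lists six classes: digestive, psychiatric, neurological, skin, urological and pain-related.
- **Statistical Analyses** gives the analysis: "Occurrence of AEs will be compared in the two groups using a Fisher's test with a significance threshold = 0.05". It states no effect measure, interval or safety margin. The next sentence plans 95% confidence intervals for the responder and continence proportions.
- **Sample Size** bases the number of patients on bladder capacity alone: "To obtain a power of 0.9 with a type I error risk set at 0.05, 26 patients per group are needed", and then "we rounded up the total expected sample size to 60". No AE rate is given for either arm.
- **Implications** looks ahead to how the safety result may be used: "If efficacy and safety are demonstrated in this population, future studies should be designed to evaluate IVO in younger children".

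**The concern.** A test of no difference answers whether an excess of AEs is large enough to be seen. It does not say how large an excess the data still allow, and a judgement on safety needs the second answer. In a trial sized for a continuous efficacy outcome, a non-significant Fisher test is the likely result even when the drug raises the AE rate appreciably.

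The article states no other criterion by which safety could be judged. If p > 0.05 were taken as reassurance, the trial could be cited in support of studies in younger children while its data remained compatible with a substantial excess of harm. The test can also hide a signal: a p-value just above 0.05 would be reported as no difference.

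**Working it through.** **Inputs.** The total is 60 (Sample Size), and Population and Sampling says "Patients will be randomised to IVO vs placebo with a 1:1 allocation", so there are 30 per arm. The test is Fisher's at 0.05 (Statistical Analyses). The article does not say whether it is one- or two-sided; two-sided is assumed. AE rates are assumptions, shown over a range. All 60 children are assumed to be analysed.

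**Step 1. The plan's own figure.** The article states: "we expect a 33% increase in maximum bladder capacity in the treated group, a 5% increase in the placebo group". It takes baseline capacity to average 170 mL with an SD of 80 mL, and the within-patient correlation to be 0.8.

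- Difference in mean change: (0.33 - 0.05) × 170 = 47.6 mL.
- SD of change: 80 × √(2 × (1 - 0.8)) = 50.6 mL.
- n per group = 2 × (1.960 + 1.282)² × 50.6² / 47.6² = 23.8, so 24; the noncentral t calculation gives 25.

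The stated 26 is reproduced to within two patients. The size is therefore sound for bladder capacity, but it was not derived from any safety quantity.

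**Step 2. Power of the Fisher test for a fixed absolute excess.** With a Binomial(30, p1) count on IVO and a Binomial(30, p0) count on placebo,

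power = Σx Σy P(X = x) P(Y = y), summed over those of the 31 × 31 tables with Fisher p ≤ 0.05.

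For an excess of 20 percentage points:

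| Placebo rate | IVO rate | Power |
|---|---|---|
| 5% | 25% | 44% |
| 10% | 30% | 37% |
| 20% | 40% | 30% |
| 30% | 50% | 26% |
| 40% | 60% | 26% |
| 50% | 70% | 26% |

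A 20-point excess is one additional affected child for every five treated. It goes undetected in 56% to 74% of trials. For a 15-point excess, power is 15% to 24% over the same placebo rates. If only 26 per arm were analysed, power for a 20-point excess would fall to 21% to 40%.

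**Step 3. Power for a tripled rate.** Here the answer depends on the unknown base rate.

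| Placebo rate | IVO rate | Power, two-sided | Power, one-sided |
|---|---|---|---|
| 5% | 15% | 9% | 17% |
| 10% | 30% | 37% | 49% |
| 15% | 45% | 65% | 76% |
| 20% | 60% | 85% | 91% |

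Two-sided power passes 50% at a placebo rate of about 12%.

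**Step 4. What the p-value leaves out.** Newcombe 95% limits for the risk difference d = p1 - p0 combine the Wilson limits (l, u) of each arm:

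lower = d - √((p1 - l1)² + (u0 - p0)²), upper = d + √((u1 - p1)² + (p0 - l0)²).

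For 9/30 on IVO and 3/30 on placebo, the Wilson limits are 0.167 to 0.479 and 0.035 to 0.256.

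- Lower: 0.20 - √(0.133² + 0.156²) = -0.005.
- Upper: 0.20 + √(0.179² + 0.065²) = 0.390.

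| IVO | Placebo | Fisher p | Risk difference (95% CI), points |
|---|---|---|---|
| 9/30 | 3/30 | 0.10 | +20 (-0.5 to +39) |
| 3/30 | 3/30 | 1.0 | 0 (-17 to +17) |
| 5/30 | 0/30 | 0.052 | +17 (+2 to +34) |

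With no event in 30 children, the exact two-sided 95% upper limit is 1 - 0.025^(1/30) = 11.6%.

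**The case against.** Five points can be made for the plan.

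- **The test is not weak everywhere.** A reader might infer that it misses even a tripled AE rate in most trials. That holds only when the placebo rate is below about 12%, and the article gives no rate. The stated test concerns AE occurrence across several classes, and Safety Profile expects instillation-site pain, urgency and urinary tract infection in both arms, so a low any-AE rate cannot be presumed. This limit stands. The result for an absolute excess of 20 points does not depend on it.
- **The sentence under Implications is conditional.** A reader might infer that the trial intends to declare safety from a non-significant test. The article never says so; it states a condition for future studies. This also stands. What remains is that no stated analysis could satisfy the condition.
- **Tolerability is analysed elsewhere.** A reader might infer that the Fisher test is the only between-arm safety analysis. It is not: intolerable side effects count towards time to treatment failure, compared by log-rank, and responder status requires their absence. Both are composites driven mainly by efficacy, however, so an effective drug could improve them while raising AE rates. The safety board's oversight is not an end-of-trial comparison.
- **This is a condensed article.** Intervals may be in the full protocol or analysis plan, and this section names none for the primary model or the Wilcoxon comparisons either. Silence alone would therefore be no finding. But the article does publish a significance rule for harm, and its next sentence names intervals for other proportions.
- **The article uses the verb describe loosely.** Objectives also uses it for voiding-diary, urodynamic and ultrasound changes, all of which are then tested. This weakens the mismatch with Objectives as an argument in itself, but not the argument from power and precision.

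**Conclusion.** The point holds in limited form. The one analysis stated for AE occurrence is a significance test with no estimate or interval. It suits a descriptive aim poorly, and a non-significant result from it could not support a statement that safety was demonstrated. Power for a 20-point excess is 26% to 44% at placebo rates of 5% to 50%, and even identical counts of 3/30 leave an excess of 17 points within the 95% interval.

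These figures rest on assumed AE rates, a two-sided test and 30 children analysed per arm. The point should be corrected, but it does not affect the primary analysis or the sample size for bladder capacity.

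**What to change.** In Statistical Analyses, replace the Fisher significance rule by estimation:

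1. Report for each arm the number of children with at least one AE, and the risk difference (IVO minus placebo) with its 95% confidence interval, for example Newcombe. Do this overall and for each AE class listed under Endpoints.
2. Where an arm has no event, give the exact upper confidence limit.
3. Keep Fisher p-values, if wanted, as descriptive, and state that p > 0.05 is not evidence of no excess harm.
4. Under Implications, tie the safety wording to the confidence limits.

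The change uses data already to be collected and needs no extra patients or visits. It adds a few rows to the safety table. The downside is that the intervals will be wide and the safety claim correspondingly weaker.

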Occurrence of adverse events (AEs; including digestive, psychiatric, neurological, skin, urological and pain‐related disorders) and their time of onset, as recorded by the patient in his/her treatment journal (Data S1) or by the practitioner during follow‐up visits.Proportion of responders, i.e., patients who had a ≥50% reduction in urinary incontinence episodes recorded in their voiding diary [20], after 4 weeks of treatment, with no intolerable AEs.Proportion of continent patients, i.e., patients who had a 100% reduction in urinary incontinence episodes, after 4 weeks of treatment [20].Standardised difference in patient's quality of life, as assessed by changes in the International Consultation on Incontinence Questionnaire‐Urinary Incontinence Short Form (ICIQ‐UI‐SF) [21] and the 10‐item KIDSCREEN questionnaire (KIDSCREEN‐10) [22] scores between the inclusion visit and the end of follow‐up.Changes in voiding diary parameters, as assessed by the change in the number and volume of urinary catheterisations over 72 h during the week preceding each follow‐up visit. If treatment is effective, voided volume should increase.Changes in urodynamic parameters between the reference cystomanometry and the cystomanometry performed at the end of treatment:
Bladder compliance (mL/cmH_2_O),Minimum filling volume causing uninhibited detrusor contraction,Detrusor leak point pressure (cm H_2_O),Volume of bladder filling during urine loss (mL).

To ensure consistency and standardisation across centres, all participating investigators will be asked to perform both cystomanometries under the same conditions for each patient, regarding bladder filling rates and patient positioning.
Changes in renal ultrasound parameters between the reference renal ultrasound (performed <2 months prior to treatment initiation), and the one performed at the end of treatment:
Pyelon anteroposterior diameter (mm),Ureter diameter (mm).

If treatment is effective, a reduction in both diameters could be observed, as a result of the decrease of pressure in the renal system.
Usability of the product, measured by the Usability Metric for User eXperience (UMUX)‐LITE scale [23] coupled with seven ad hoc questions specific to the treatment and disease under study, measured on a 7‐point Likert scale (from strongly disagree to strongly agree; Data S2).

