### Safety Profile

All patients included in the study will have already received oral anticholinergic treatment, which reduces the risk of allergy to oxybutynin. In addition, any contraindication to the use of oral anticholinergic treatment also contraindicates participation in the present study, which should reduce the risk of serious AEs (SAEs).

Intravesical administration is associated with better bioavailability of oxybutynin compared to oral administration, as there is no first intestinal passage. This results in a reduction of its main metabolite, N‐desethyloxybutynin, which is less effective and has significant side effects [24]. Previous studies showed that the occurrence of adverse effects was lower with intravesical administration, as compared with oral oxybutynin [11, 15, 25, 26, 27, 28]. In the study by Schröder et al. [11], the adverse effects specifically found in the IVO group were: pain at the instillation site, headaches, abdominal pain, urinary urgency, decreased sweating, and hypotension. The adverse effects found in both modes of administration of oxybutynin were: dry mouth, constipation, dizziness, fatigue, dry eyes, attention disorders, drowsiness, apathy, and delayed urination. Finally, the expected risks of intravesical instillation, both for the oxybutynin and placebo groups are as follows: pain at the instillation site, urinary urgency and UTI.

Adverse effects will be systematically documented at each visit using the treatment journal. In case of fever, the patient will be prescribed an emergency urine culture. If positive, the patient will be urgently referred to a doctor at his/her centre to assess the need for antibiotics.

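### The one between-arm adverse event test, read as any event, mixes instillation events expected in both arms with systemic anticholinergic effects and so loses power to show an excess of the latter on IVO

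*Protocol article*

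**What the plan says.** The Objectives section lists safety as a descriptive aim: "To describe treatment tolerance and adverse effects". The Endpoints section defines the outcome as the occurrence and time of onset of adverse events, "including digestive, psychiatric, neurological, skin, urological and" pain-related disorders, recorded in the patient's treatment journal or by the practitioner at visits. The Statistical Analyses section then fixes the comparison in one sentence: "Occurrence of AEs will be compared in the two groups", by Fisher's test at 0.05. It does not say whether the unit is any event, a class of events or a defined group, and it names no other between-arm adverse event comparison.

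The Safety Profile section distinguishes kinds of event. It says that "the expected risks of intravesical instillation, both for the oxybutynin and placebo groups are as follows: pain at the instillation site, urinary urgency and UTI". It separately lists effects that an adult trial found with both oral and intravesical oxybutynin: "dry mouth, constipation, dizziness, fatigue, dry eyes, attention disorders, drowsiness, apathy, and delayed urination". A third list, of effects found specifically with intravesical use in that trial, includes site pain and urgency as well as decreased sweating and hypotension.

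**The concern.** If the test counts children with at least one event of any kind, a placebo child with a urinary tract infection weighs the same as an actively treated child with drowsiness. A child already counted for an instillation event adds nothing when a drug effect follows. The shared events raise both arms' rates and shrink the difference that the test sees.

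This matters because systemic tolerance is part of the case for the intravesical route. The Background cites cognitive and other side effects of oral dosing, and the Safety Profile section argues that they are less frequent with instillation. A non-significant test on any event could be read as reassurance about systemic effects when it says little about them.

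**Working it through.** **The plan's own figures.** The protocol states no power or sample size for the adverse event comparison. Its only calculation is for bladder capacity: 26 per group, rounded up to 60 in total. That calculation can be approximated:
- Difference = 170 × (0.33 − 0.05) = 47.6 mL.
- SD of change = 80 × √(2 × (1 − 0.8)) = 50.6 mL.
- At two-sided 0.05 and power 0.90 this gives 24 per group (normal) or 25 (t-test), close to the stated 26.

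With 60 children and 1:1 allocation, the adverse event test has 30 per arm.

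**Inputs for the safety test.**
- From the protocol: Fisher's test, threshold 0.05, 30 per arm.
- Assumed: a two-sided test; drug-type event rate d in each arm; shared instillation event rate s, equal in both arms; the two kinds of event independent within a child. The protocol gives none of these rates.

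**Formula.** Rate of any event = 1 − (1 − d)(1 − s). Power is the exact probability of p ≤ 0.05, summed over all pairs of counts from two binomials of size 30.

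**Example.** With d = 5% on placebo and 40% on active treatment, and s = 50%:
- Placebo: 1 − 0.95 × 0.50 = 0.525.
- Active: 1 − 0.60 × 0.50 = 0.70.
- The difference shrinks from 35 to 17.5 percentage points, and power falls from 0.89 to 0.20.

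**Results (power).**

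| Drug-type events, placebo v active | Those events alone | Any event, s = 10% | s = 30% | s = 50% | s = 70% |
|---|---|---|---|---|---|
| 5% v 20% | 0.24 | 0.16 | 0.08 | 0.05 | 0.04 |
| 5% v 30% | 0.63 | 0.41 | 0.20 | 0.11 | 0.06 |
| 5% v 40% | 0.89 | 0.69 | 0.38 | 0.20 | 0.10 |
| 10% v 60% | 0.99 | 0.93 | 0.72 | 0.44 | 0.20 |

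Pooling lowers power in every row. The loss is modest when shared events are few and the excess is very large, and severe when shared events are common. The first row shows a separate limit: with 30 per arm, a small excess is hard to detect even without dilution. About 5% against 36% is needed for power of 0.80 on drug-type events alone.

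**If the test were run by class instead.** The result depends on how the effects fall across classes. Suppose the 5% v 40% total is split evenly over k independent classes, each with rate 1 − (1 − d)^(1/k). Power per class is then 0.49 for two classes, 0.22 for three and 0.10 for four. If instead one class carried 3% v 30%, its power would be 0.75. Six independent tests at 0.05 without adjustment would carry a familywise error of 1 − 0.95⁶, about 0.26.

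**The case against.** The strongest objection is that the protocol never says the test is on any event. The Endpoints section names classes, so a by-class comparison is open, and the unit of tabulation may be set in a full protocol or analysis plan not shown here. This stands as a limit: "any event" is the most direct reading, not a stated rule. The by-class reading would avoid much of the dilution if drug effects cluster in one or two classes. It would not do so reliably, because the effects named in the Safety Profile section could spread over several classes, and urgency and infection would share the urological class with delayed urination.

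A reader might infer that shared events will swamp the comparison and that a real excess is likely to be missed. The documents do not support that. They give no rates, and under some assumptions the pooled test keeps power of 0.93. Nor would one non-significant result hide an excess by itself: the objective is descriptive, event type and onset are recorded, intolerable effects also enter treatment failure and responder status, and an independent safety board oversees the trial.

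A reader might also infer that the class list omits hypotension, dry eyes and fatigue. The list opens with "including", so it is illustrative and excludes nothing.

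Finally, the Safety Profile section supplies no ready-made systemic group. Its list of effects specific to intravesical use puts site pain and urgency beside hypotension and decreased sweating. Any grouping is therefore a judgement to be agreed, and dropping the between-arm comparison of site pain and urgency would lose information.

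**Conclusion.** The point holds in a limited form. The only between-arm adverse event test in the protocol, on its most direct reading, pools events that the protocol itself expects in both arms with the systemic effects of the drug. The direction of the loss is clear; its size is not. For 5% v 40% drug-type events, power falls from 0.89 to between 0.69 and 0.10 as the shared rate goes from 10% to 70%. These figures rest on assumed rates, independence of the two kinds of event, a two-sided test and 30 children per arm. Small numbers are a separate weakness that removing the dilution does not cure. This is an inexpensive improvement to the analysis, not a fault that invalidates the safety assessment.

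**What to change.** In the Statistical Analyses section, fix before unblinding a list of systemic anticholinergic effects drawn from those named in the Safety Profile section. It could cover, for example, constipation, dry mouth, dry eyes, decreased sweating, fatigue, drowsiness, dizziness, apathy and attention problems. Assign borderline events, such as abdominal pain or delayed urination, in advance. Compare between arms the number of children with at least one listed event that starts or worsens after the first instillation.

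Keep the by-arm reporting of instillation events (site pain, urgency, urinary tract infection) and of any event beside it. State that a non-significant result for any event is not evidence that systemic effects are absent. The classes in the Endpoints section need no change.

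The cost is a short agreed event list and one more comparison. The treatment journal and visits already collect the data.

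### The log-rank and Wilcoxon tests are specified without the age stratum used in randomisation: still valid, but conservative and less powerful to the extent that age is prognostic

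*Protocol article*

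**What the plan says.** All references are to the protocol article.

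- **Population and Sampling.** Randomisation is "stratified by age group (6–11 years, ≥12 years) with the use of a permuted block design of size 10", with 1:1 allocation.
- **Statistical Analyses, primary outcome.** Change in maximum bladder capacity is analysed "using a linear mixed model accounting for repeated measurement, age stratification, and treatment exposure as a binary variable".
- **Statistical Analyses, first ordered secondary (maximum bladder pressure).** Here "the two groups will be compared using the same methodology as for the primary outcome", so the stratum carries over.
- **Statistical Analyses, second ordered secondary (time to treatment failure).** Here "the two groups will be compared using a two‐tailed log‐rank test". No stratum is named.
- **Statistical Analyses, other changes.** Quality-of-life differences are given a Wilcoxon test at 0.05, and likewise: "Changes in voiding diary elements, urodynamic parameters, and renal ultrasound parameters after 4 weeks of treatment will be compared using a Wilcoxon test". No stratum is named in either place.

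An exploratory linear regression is adjusted for age and gender, but it is described alongside the primary outcome and is not part of the secondary tests.

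**The concern.** Stratified randomisation balances age between the arms, so age differences contribute little to the chance variation of the treatment contrast. A test that ignores the stratum still counts the spread between age groups as noise. Its standard error is then too large, its true type I error falls below 5% and it loses power. For the log-rank test, mixing two age groups with different hazards also dilutes the treatment effect being tested.

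The test that matters most is the log-rank. It is the last of the ordered hypotheses and sits in the same fixed sequence as bladder pressure, which does use the stratum. With 60 children and a limited number of failures, its power is modest to begin with. The Wilcoxon endpoints lie outside that sequence and matter less.

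Age could plausibly be related to these outcomes. The maximum daily dose changes at the stratum boundary of 12 years (Intervention), and cystomanometric filling may stop at the volume expected for age (Endpoints). Neither fact measures how strong the relation is.

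**Working it through.** **1. The plan's own figure.** Sample Size assumes increases of 33% and 5% on a mean of 170 mL, SD 80 mL and correlation 0.8.

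- Difference: 0.28 × 170 = 47.6 mL.
- SD of change: 80 × √(2 × (1 − 0.8)) = 50.6 mL.
- n per group, two-sided 0.05 (sidedness assumed), 90% power: 2 × (1.960 + 1.282)² × 50.6² / 47.6² ≈ 24, or 25 using the t distribution.

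The stated 26 per group is therefore reproduced closely; power is about 92% at 26 and 95% at 30 per group. This calculation concerns only the primary outcome, whose model uses the stratum, so it is not affected.

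**2. Log-rank test.** From the article: 60 patients, 1:1, two age strata, 28 days. Assumed, because the article gives none: about 30 patients per stratum, exponential failure times, treatment hazard ratio 0.4, and the control hazards and age effects below.

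Power, plain / stratified (2,000 simulated trials per cell; Monte Carlo standard error about √(0.7 × 0.3 / 2000) = 1 point):

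| Control hazard | No age effect | 2-fold | 3-fold | 5-fold |
|---|---|---|---|---|
| 0.04/day, midway (geometric mean) between strata | 71 / 71% | 68 / 72% | 64 / 72% | 55 / 73% |
| 0.04/day in the higher-risk stratum, lower in the other | – | 59 / 62% | 52 / 57% | 46 / 53% |
| 0.08/day on average | – | 83 / 86% | 74 / 83% | 60 / 83% |

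The loss is 3–4 points at 2-fold, 5–9 at 3-fold and 7–23 at 5-fold. A wider set of nine hazard settings gave about 0–2 points at 1.5-fold and 1–4 points at 2-fold. Rows differ mainly through the number of failures. In the first row with no age effect, the expected number is 30 × (1 − e^(−0.04×28)) + 30 × (1 − e^(−0.016×28)) = 30 × (0.674 + 0.361) ≈ 31; in the second row it is about 20–25.

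A larger run (12,000 trials per setting, 0.04/day in the higher-risk stratum, blocks of 10) gives the type I error as well:

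| Hazard ratio between age strata | Type I error, plain / stratified | Power, plain / stratified |
|---|---|---|
| 1 | 5.6 / 5.4% | 71 / 70% |
| 0.6 | 4.2 / 4.7% | 63 / 64% |
| 0.4 | 3.9 / 5.2% | 55 / 58% |
| 0.25 | 2.9 / 4.7% | 47 / 53% |

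The slight excess over 5% in the first line appears in both tests and without any age effect, so it does not come from ignoring the stratum.

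**3. Wilcoxon test.** Assumed: normal outcomes, treatment effect 0.85 SD, 60 patients, blocks of 10, 6,000 trials per setting. With equal strata, an age difference of d SD explains (d²/4) / (1 + d²/4) of the variance.

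| Age difference | Variance explained | Type I error, plain / van Elteren | Power, plain / van Elteren |
|---|---|---|---|
| 0 | 0% | 5.1 / 5.2% | 88 / 88% |
| 0.5 SD | 6% | 3.9 / 4.7% | 87 / 88% |
| 1.0 SD | 20% | 3.1 / 5.2% | 83 / 88% |
| 1.5 SD | 36% | 1.2 / 4.5% | 73 / 87% |

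The loss is nil, about 1, 5 and 14 points respectively. In both test families, stratifying when age has no effect costs less than 1 point.

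**The case against.** The strongest reply is that this is a condensed article. It gives one phrase per test, and a full analysis plan may well name stratified versions. That possibility stands, and if so the remedy is only to confirm it. It does not remove the point: the article mentions the stratum where it is used, and it describes the tests of two neighbouring ordered hypotheses, one with the stratum and one without.

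The second reply is that nothing here is invalid. That is right. A reader might infer that ignoring a stratification factor endangers the error rate. Here the effect runs the other way: the tests become conservative, and no extra false positives arise.

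The third reply concerns size. A reader might infer a certain and substantial loss of power because the sponsor chose to stratify on age. The article gives no reason for that choice and no estimate linking age to treatment failure, a composite of perceived inefficacy, insufficient reduction in leakage and intolerable effects. Most Wilcoxon endpoints are within-patient changes, which may remove part of any age difference. Power was planned only for the primary outcome. All of this stands, and it limits the point to a modest, conditional gain.

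**Conclusion.** The point holds as an efficiency matter of low severity. The log-rank test for time to treatment failure and the Wilcoxon tests for the secondary changes are specified without the randomisation stratum, unlike the two mixed-model analyses. Under the assumptions shown, the log-rank loss is nil if age is not prognostic, about 0–4 points for an age hazard ratio of 1.5–2, and roughly 5–9 points at 3-fold. Losses beyond 10 points appeared only at 5-fold (log-rank) or at an age difference of 1.5 SD (Wilcoxon). These figures rest on assumed hazards, treatment effects and equal strata; the article supports none of them directly. The documents do not support a claim of invalid inference, of a known power loss, or of any effect on the primary analysis or the sample size.

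**What to change.** In Statistical Analyses, state that time to treatment failure will be compared by a two-tailed log-rank test stratified by the randomisation age group (6–11, 12 years or over). State also that the quality-of-life, diary, urodynamic and ultrasound changes will be compared by van Elteren's test with the same strata. If the full analysis plan already says this, confirm it; if the stratum is left out on purpose, give the reason.

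Replacing the Wilcoxon tests by a baseline-adjusted linear model would be a separate decision about baseline adjustment and distributional assumptions. It does not follow from this point.

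The cost is wording only. Age group is recorded for every child at randomisation, no extra data or patients are needed, and the power given up if age turns out not to matter is about 1 point at most. The change should be fixed before unblinding.
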